**Respiratory Measures**

Respiratory rate will be measured twice for each participant to reduce within-session variability. It will be determined by counting the number of inhalations with a stethoscope for 30 seconds at rest and multiplying by two at baseline and post-intervention (Lim et al., 2002). (Normal adult rate is 12 to 18 breaths/minute).

**AYT *Treatment Validation***

Four measures will be collected to assess the benefits of the AYT, compliance, fidelity of treatment and evaluate the participant’s experience.

1. The *Philadelphia Mindfulness Scale* (PHLMS). This 20-item scale assesses two components of mindfulness, *acceptance* and *awareness*. Total scores on both subscales range from 20 to 100, higher scores reflect greater mindfulness. The PHLMS will be collected at baseline, during week 4 and post- intervention. The PHLMS shows good internal reliability as reported in clinical and non-clinical samples. Total scores on both subscales range from 20 to 100, higher scores reflect greater mindfulness. This scale was chosen because the two components are orthogonal, or independent. Interestingly, *acceptance* is associated with reduced depression, anxiety and rumination but is unrelated to *awareness.* Thus, the PLHMS will allow us to determine distinct benefits associated with *mindfulness* induced by the yoga intervention.

2. *Practice/Homework Logs.* Participants will be asked to complete a weekly log online to report the activity performed, time allotted to the practice and will be used to evaluate compliance.

3. *Treatment Fidelity.* The yoga sessions will be videotaped and a treatment observation log by an independent observer (e.g. research assistant) will be completed during 4-6 yoga sessions chosen randomly to confirm adherence to the yoga treatment.

4. *Exit survey.* Participants will complete a brief, anonymous survey regarding their experience with the AYT. The survey is comprised of open-ended and multiple-choice response items (e.g. treatment expectations).

**Intervention Phase**

*Ashtanga-based Yoga Therapy*. The AYTincludes one session a week with the instructor (i.e. [name]) and participants will additionally be asked to perform at least two home-based practice sessions per week for a total of 8 weeks. An orientation session will be conducted during the baseline period prior to the intervention to familiarize subjects with yoga basics that include: Alignment, Breathing, Set up, Supplies, Journaling, and Room Temperature. Several studies have successfully used an 8-week period that produced positive outcomes. Participants will be led through the sequence of postures and the instructor will make adjustments and answer questions as needed. Participants will be asked to continue a home-practice twice a week. An audio CD will be provided to facilitate the home practice and ensure duration and compliance to the sequence. All participants will be encouraged to keep a journal either on the computer or with the help of a sighted companion. Interactions with the instructors and keeping a journal are meant to encourage compliance. Intervention sessions will be held in small groups if possible, or individually if necessary due to scheduling issues.

*Study Outcome Measures.*All outcome measures will be administered at baseline and post-intervention. Mood questionnaires will additionally be measured during week 4. The PHLMS will be collected at 3 time points, baseline, week 4 and post-intervention. The online questionnaires administered weekly during the intervention will include the Perceived Stress Scale (PSS) and the Positive and Negative Affect Schedule (PANAS). Participants will be asked to complete a weekly practice logs online to report the activity performed, time allotted to the practice and will be used to evaluate compliance. Participants will complete a brief exit survey online regarding their experience with the AYT. The survey is comprised of open-ended and multiple-choice response items (e.g. treatment expectations).

1. ***Study duration and number of study visits required of research participants.***

The pilot study will be completed over the course of 4-6 months. The intervention phase will be conducted over the course of 12 weeks and will require 12 study visits. The baseline period will be used to collect the full Baseline Assessment Battery and assign the Sleep Diaries. The orientation session will be conducted on the same day as the first class. Post-intervention (i.e. after 9-weeks) will consist of a two-week period to collect the Post-Assessment Battery (all measures from baseline) and assign the Sleep diaries. The waitlist control will begin the yoga treatment after pre- and post- measures have been obtained during the first round of testing. The final set of post-tests after the waitlist group has completed the 8-week yoga class, will allow us to compare effect of AYT on the two groups, and determine retention of any gains from the first AYT block.

1. Blinding, including justification for blinding or not blinding the trial, if applicable.

N/A

1. Justification of why participants will not receive routine care or will have current therapy stopped.

N/A

1. Justification for inclusion of a placebo or non-treatment group.

All enrolled participants will eventually receive the AYT intervention.

1. Definition of treatment failure or participant removal criteria.

Subjects may be removed from the study if they demonstrate lack of cooperation by repeatedly missing appointments, or by providing highly inconsistent responses that suggest lack of concentration.

1. Description of what happens to participants receiving therapy when study ends or if a participant’s participation in the study ends prematurely.

There are no consequences to participants if they leave the study early or are removed from the study for non-compliance.

1. **Inclusion/Exclusion Criteria**

Inclusion criteria:
- Age 18+

- Legal blindness (visual acuity worse than 20/200 but better than no/bare light perception, and/or visual field less than 20º, in the better eye)

- Any ocular disease diagnosis that is expected to remain relatively stable throughout a 3-6 month period

- Being healthy to the extent that participation yoga therapy would not exacerbate any existing disease conditions;

- Willingness to participate on a weekly basis for the 12-week intervention;

Exclusion criteria:

- Significant changes to vision within the most recent 3-month period

- Inability to understand study procedures or communicate responses to visual stimuli in a consistent manner

-Vestibular problems

-Symptomatic cardiovascular disease

-poorly controlled blood pressure

-history of neurologic disease

-acute orthopaedic problems that affect ambulation

-metastatic cancer

-pregnant women

1. **Drugs/ Substances/ Devices**
2. The rationale for choosing the drug and dose or for choosing the device to be used.

N/A

1. Justification and safety information if FDA approved drugs will be administered for non-FDA approved indications or if doses or routes of administration or participant populations are changed.

N/A

1. Justification and safety information if non-FDA approved drugs without an IND will be administered.

N/A

1. **Study Statistics**
2. Primary outcome variable.

The primary outcome variables are objective and subjective measures of sleep and balance for participants with low vision.

1. Secondary outcome variables.

Secondary measures include FOF, psychosocial mood, AYT validation, physical function and respiratory measures across all subjects.

1. Statistical plan including sample size justification and interim data analysis.

Baseline demographics and clinical variables will be summarized and compared for the 2 groups using descriptive statistics and parametric or non-parametric tests as appropriate. *Primary analysis:* Multiple regression analyses will determine the relationship between vision loss and sleep disturbances. We hypothesize that measures of vision function will be the best predictors of sleep disturbance after accounting for age, general health and psychosocial factors.

Group differences (e.g. age, level of fitness) will be used as covariates in the main intervention analysis. Group differences during post-intervention assessment will be estimated using a multivariate analysis of covariance (ANCOVA), with the baseline measures as covariates. Groups will be compared for the primary, as well as secondary measures. *Secondary Analyses:* A multiple regression analysis will be conducted to determine whether impaired visual function (VA, CS, VF) can predict the outcomes for static and FoF while controlling for age and fitness. A post-hoc analysis will determine whether subgroups (e.g. congenital blindness vs. acquired blindness) or other prognostic factors can reliably predict outcome measures. To assess the AYT, items from the exit survey will be evaluated and summarized to reveal patterns in the subjects’ overall experience. Practice logs will give us information related to compliance, total practice time during the week, and progress in terms of difficulty over the course of the 8 weeks. Treatment fidelity is determined by AYT adherence as measured by the observation log.

A sample size calculation is not applicable to this type of exploratory, pilot study, however, a minimum of 10 subjects is feasible to provide an indication of the acceptability of the AYT intervention and to help suggest possible benefits across a moderate-sized group of visually-impaired subjects. It will also allow us to further develop the intervention protocol and plan for larger scale RCTs as indicated.

1. Early stopping rules.

N/A

1. **Risks**
2. Medical risks, listing all procedures, their major and minor risks and expected frequency.

The vision tests we plan to evaluate do not entail any risks and we do not anticipate any study related adverse events or injuries related to them. In the case that a subject experiences a significant change in vision between visits, a dilated eye examination will be performed in order to determine the cause of the change, and/or appropriate referrals will be made as needed.

To minimize the discomfort associated with completing study questionnaires and diaries, subjects will be informed that they are free to refrain from answering any questions that make them uncomfortable of that they perceive as being personal or sensitive and do not wish to share as part of the study. If information gathered through the research indicates that a participant needs urgent psychiatric care (e.g. expressed suicidality), Drs. [name] and [name] will be immediately notified and the subject will be referred for immediate care.

Prior to the intervention, participants will notify the instructor of all pre-existing physical injuries.

The instructor will note each condition for each subject and suggest modifications for each pose based on subjects’ responses. To reduce the risk of injury, subjects will be advised to never force or strain themselves during exercise. If subjects feel pain, they will be advised to stop immediately and seek medical attention if necessary.

Testing of physical abilities through Balance and Physical function tests pose a very small possibility of falls or injury. However, subjects who feel uncomfortable can opt out of the balance tests. Research coordinators administering the tests are trained to identify individuals who may be at risk of injury during testing and will not perform tests on subjects for whom they feel testing would be unsafe. Coordinators will be trained in methods to prevent injury in cases where a subject loses his/her balance or begins to fall. No injuries have occurred in over 200 individuals tested with this protocol in other studies at the Wilmer Eye Institute and in over 10,000 subjects studied in other protocols[19](#_ENREF_19).

Another risk that requires management is the potential breach of patient confidentiality. The study investigators have been trained in the methods necessary to protect subjects’ privacy and every attempt will be made to maintain records and data in secure databases and areas. This study poses minimal additional risk. The societal benefits outweigh these risks.

1. Steps taken to minimize the risks.

If dilating drops are used, study personnel are trained in detecting ophthalmic adverse effects, including acute glaucoma.

1. Plan for reporting unanticipated problems or study deviations.

In the very unlikely event that a serious adverse event occurs, the study co-investigator(s) will immediately notify the IRB within 24 hours of the occurrence, using the standard JHU Adverse Event report form.

1. Legal risks such as the risks that would be associated with breach of confidentiality.

N/A

1. Financial risks to the participants.

N/A

1. **Benefits**
2. Description of the probable benefits for the participant and for society.

There will be no direct benefit to the subjects as a result of performing the vision tests, questionnaires, or balance tests. We will share the results of the vision tests with the subjects. At the end of the study, subjects’ visual status will be monitored for any significant changes by a licensed clinician, which may be considered a benefit. Any new information regarding the subjects’ vision may be shared with their eye care provider, at the subjects’ request.

Potential benefits may occur during the yoga intervention; however, this has not been previously demonstrated with scientific study among this patient population. Other types of patient populations have experienced decreased stress, anxiety, fatigue, depression, improved balance, and sleep as a result of yoga interventions. The anonymous exit surveys may allow the subjects to learn more about the experiences of other visually impaired subjects as a result of their AYT practice.

1. **Payment and Remuneration**
2. Detail compensation for participants including possible total compensation, proposed bonus, and any proposed reductions or penalties for not completing the protocol.

Participants will receive a free yoga mat and AYT instruction, as well as parking validation if they travel to our center with a sighted companion.

1. **Costs**
2. Detail costs of study procedure(s) or drug (s) or substance(s) to participants and identify who will pay for them.

The subjects will not be responsible for any costs directly related to the project, with the exception of transportation-related costs to our center.

Funding is provided by a scholarship from the Delta Omega public health honor society and by the [name] Wilmer Research Grant.

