1) To explore the relationship between psychophysical visual function in patients with severe vision loss and sleep disturbances, negative psychosocial factors and balance.

2) To test the feasibility of a yoga intervention for reducing secondary symptoms.

3) To determine the use of a commercially available Nintendo Wii Balance BoardTM (WBB) to measure static balance in visually impaired individuals.

1. **Background** (briefly describe pre-clinical and clinical data, current experience with procedures, drug or device, and any other relevant information to justify the research)

**Yoga as an approach.** Yoga has been shown to be a viable intervention for improved sleep disturbances, mood disturbances, fear of falling (FOF), and balance, in healthy individuals or those with other chronic diseases. Yoga is an integrated system of postures, movement, breath and meditation and is easily implemented regardless of age or level of experience. The Ashtanga-based Yoga Therapy (AYT)will be evaluated for its feasibility. The main component of the AYT is movement with the breath. The breathing involved, called *ujjayi* breathing, is a specialized technique that emphasizes use of the diaphragm. Poor breathing patterns can lead to anxiety and chronic overstimulation of the sympathetic nervous system in emphysema patients. On the other hand, normal, healthy breathing can influence cardiovascular factors producing a stabilizing effect. Teaching yoga to low vision patients requires simple modifications to postures, clear descriptions, and hands-on adjustments.

**Sleep disturbances and psychophysical measures***.* Very little is understood about the relationship between psychophysical measures (visual field, contrast sensitivity, acuity) and sleep disturbance as VI progresses. Measuring relative rod and cone sensitivities with a two-filter dark-adapted ganzfeld test system will determine the extent of retinal degeneration.

**Yoga and Psychosocial Factors***.* The impact of visual loss on negative mood states (e.g. anxiety,

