**AYT Validation.** The purpose of yoga is to integrate mind and body and therefore incorporates a contemplative or mindfulness component that sets it apart from regular exercise. ‘Mindfulness’ in this setting promotes self-awareness in a non-competitive, non-judgmental environment and at the same time promotes awareness to muscular movements, alignment and the breath. Study patients are more likely to comply with an intervention if it is safe, engaging and easy to follow. Therefore, measuring compliance with practice logs and participant experience through exit surveys will further help evaluate the yoga intervention. Finally, evaluating the fidelity of treatment or how accurately the yoga protocol is reproduced will be a step forward in the effective standardization of the AYT as a means of improving quality of life in VI. We will videotape and/or photograph all yoga sessions and randomly select 4-6 classes for scoring. Fidelity is based on how closely the instructor adhered to the yoga protocol (i.e. sequence of poses, duration) during the class, and will be scored according to checklist criteria, in order to provide feedback and additional training to the instructor.

In addition to assessing fidelity of treatment, these recordings and/or photographs may be shown at scientific and non-scientific professional meetings. Recordings will only be used for educational or scientific purposes with the participant’s consent.

1. **Study Procedures**
2. ***Study design, including the sequence and timing of study procedures***

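### The removal rule lets randomised subjects be dropped for missing appointments in a feasibility trial, which risks selective loss of post-tests and compliance data, mainly from the yoga arm

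*Protocol*

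**What the plan says.** Under Study Procedures, the item on treatment failure and removal criteria reads: "Subjects may be removed from the study if they demonstrate lack of cooperation by repeatedly missing appointments". A second ground is highly inconsistent responses. The item gives no threshold and does not say who decides. The following item names the ground and describes the aftermath: "There are no consequences to participants if they leave the study early or are removed from the study for non-compliance". The blinding item is answered as not applicable.

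Objective 2 is "To test the feasibility of a yoga intervention for reducing secondary symptoms". The AYT Validation paragraph of the Background says that "measuring compliance with practice logs and participant experience through exit surveys will further help evaluate the yoga intervention". The AYT Treatment Validation section lists the logs among its four measures, and Study Statistics repeats that "Practice logs will give us information related to compliance, total practice time during the week".

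For the randomised comparison, Study Statistics says: "Group differences during post-intervention assessment will be estimated using a multivariate analysis of covariance (ANCOVA), with the baseline measures as covariates". The General Overview says that post-tests are taken from every subject after the first 8-week block. The Intervention Phase section gives the AYT arm one instructor session a week for 8 weeks, while the other arm waits.

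**The concern.** Repeated non-attendance is a result that a feasibility trial needs to report. Here it is also a ground for ending a subject's participation after randomisation. Two things are at stake.

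- **Feasibility results.** A removed subject supplies no further logs, and nothing provides for an exit survey or post-test. Those who stop coming are the most informative about whether the intervention is acceptable. If they also drop out of the denominators, compliance looks better than it was.
- **The randomised comparison.** In the first 8 weeks the opportunity to miss appointments lies almost wholly in the AYT arm. Removal can therefore be selective by arm. It also rests on a judgement without a threshold, possibly made by staff who know the allocation. Adjusting for baseline does not supply outcomes that were never collected.

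**Working it through.** The protocol gives 10 as a feasible minimum, with no alpha, power, effect size or SD behind it, so there is no stated figure to reproduce. The check is a comparison of the passages followed by illustrative arithmetic.

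**Passages side by side**

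1. The rule ends study participation, not only class attendance: both items speak of removal from the study.
2. The ground is non-compliance, in the protocol's own word, and compliance is an evaluated measure.
3. The General Overview takes post-tests from every subject. No section says that removed subjects are still post-tested, and none says that they are not. The two statements are not reconciled.
4. In the first block the AYT arm has 8 weekly sessions. The waitlist arm has no classes until its own block, which comes after the first post-tests.

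**Share of an arm.** A minimum of 10 subjects in two equal groups gives 5 per arm. One removal is 1/5 = 20% of an arm.

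**Chance of at least one removal among 5** (assumption: each AYT subject independently meets the rule with probability p), 1 − (1 − p)^5:

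| p | Result |
|---|---|
| 0.1 | 0.41 |
| 0.2 | 0.67 |
| 0.3 | 0.83 |

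**Compliance proportion** (assumption: 2 of 5 AYT subjects are non-compliant, are removed, and are left out of the denominator; Clopper-Pearson intervals):

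- All allocated: 3/5 = 60%, 95% CI 15% to 95%.
- Remaining only: 3/3 = 100%, 95% CI 29% to 100%.

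**Mean class attendance** (assumption: attenders make 7 of 8 classes, non-attenders 2 of 8):

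- One non-attender in 5: (4×7 + 1×2)/40 = 75%.
- Two non-attenders in 5: (3×7 + 2×2)/40 = 62.5%.
- Among those remaining, in either case: 7/8 = 87.5%.

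**Precision** with 3 against 5 instead of 5 against 5 and equal SDs: √[(1/3 + 1/5)/(1/5 + 1/5)] = √(0.5333/0.4) = 1.155, a 15% larger standard error.

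**Bias with no true treatment effect.** Assume that a share q of each arm would be non-attenders, that their outcomes are g SD worse, and that they are removed from the AYT arm only. The retained AYT mean is 0 and the waitlist mean is −qg, so the spurious benefit is qg. Under ANCOVA, g is the difference left after baseline adjustment.

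| q | g = 0.3 | g = 0.5 | g = 0.8 | g = 1.0 |
|---|---|---|---|---|
| 0.1 | 0.03 | 0.05 | 0.08 | 0.10 |
| 0.2 | 0.06 | 0.10 | 0.16 | 0.20 |
| 0.4 | 0.12 | 0.20 | 0.32 | 0.40 |

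A simulation with 400,000 per arm at q = 0.2, g = 0.5 gave 0.099 SD with removal and −0.002 SD with everyone kept.

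**The case against.** The strongest reply is that the rule is permissive and says nothing about data handling. Logs are weekly, so records up to removal would exist, and a removal can itself be reported as a feasibility result. This stands. A reader might infer that non-compliers' data are discarded and that compliance rates will be computed on those who remain. The protocol says neither. It defines no attendance or retention rate and no denominator, and analysis sets are commonly left to an analysis plan that is not at hand. What an analysis plan cannot do is recover post-tests and logs not collected after removal, so that part belongs in the protocol.

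Second, the direction of bias is not given by the documents. If absentees were those doing better, the sign would reverse. The asymmetry is not absolute either: waitlist subjects have post-test appointments and later take the same classes under the same rule. Both points stand, so the bias towards yoga must be stated conditionally.

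Third, Objective 2 does not name compliance, which is one of several validation measures. The analysis labelled primary is a regression of sleep disturbance on vision loss, not the group comparison. This limits the consequences. It does not remove the conflict, because the group comparison is still planned for primary and secondary measures.

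Fourth, repeated non-attenders may miss post-tests anyway, so a corrected rule may recover only part of the loss.

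Finally, a reader might take the inconsistent-responses ground to duplicate the exclusion criterion "Inability to understand study procedures or communicate responses to visual stimuli in a consistent manner". The two overlap, but the exclusion concerns understanding procedures and responses to visual stimuli. The removal ground is wider and can arise during follow-up. The documents do not support treating it as redundant or confining it to baseline.

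**Conclusion.** The concern holds in a limited form. The protocol permits discretionary, threshold-free removal from the study for non-compliance after randomisation, in a trial that evaluates feasibility and compliance. In the first 8 weeks the rule bears mainly on one arm, and it is not reconciled with post-testing every subject. The risk is selective loss of post-tests and logs that later analysis cannot repair.

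The size cannot be computed from the document. Each removal costs 20% of an arm at the minimum sample. The shift from 60% to 100% compliance and the 15% larger standard error illustrate two removals in five. The first also requires that removed subjects leave the denominator, and its two intervals overlap widely. The spurious benefit of 0.03 to 0.40 SD requires removal in the AYT arm only and worse outcomes among those removed. The document establishes neither condition, so it does not support a conclusion that the comparison will favour yoga.

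**What to change.** Amend the removal item before enrolment to state that:

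- missed classes or home practice are recorded as non-compliance and do not by themselves end study participation;
- all randomised subjects are invited to every post-test, which also settles the General Overview wording, and are analysed in the group to which they were randomised;
- all subjects allocated to AYT form the denominator for compliance and study retention;
- any subject removed for inconsistent responses is reported by arm, with the reason.

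The cost is a few sentences and modest effort to bring non-attenders back for post-tests. The compliance figures may look less favourable.

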We anticipate that all procedures will take place at the Johns Hopkins Wilmer Eye Institute’s Lions Vision Center. We propose to contact potential subjects by phone and/or email to determine whether they meet the entry criteria and are interested. Enrolled subjects will first be assessed for all baseline measures and then be randomized into two equally sized groups to either start the AYT intervention immediately or to a waitlist control group receiving usual care during the initial 8-week intervention period. Waitlist control subjects will also receive the AYT intervention following the completion of the first AYT intervention group. Participants will convene weekly during the study period and [name] (or a trained instructor) will teach the AYT intervention since she has previous experience teaching yoga to visually impaired individuals. [name] will also train volunteer yoga instructors in the yoga protocol. This has been done previously in our pilot study[9](#_ENREF_9). Participants will also be asked to practice the intervention at home twice a week in addition to the visit at the center using a CD with audio instructions created by [name]. A Post-Assessment Battery (all measures from baseline) will be collected immediately following the intervention. Another set of post-tests will be administered to the waitlist group. The waitlist control group will allow us to compare the effects of AYT on the test measures to that of usual care, while the final set of post-tests will allow us to compare effect of AYT in the two groups, and determine retention of any gains from the first AYT block.

A baseline assessment batteryfor all variables of interest will be obtained during the baseline period. These measures include **visual function, sleep, psychosocial questionnaires**, **fear of falling (FOF), physical function** and **balance**. All baseline measures will be reassessed within two weeks after the AYT intervention has been completed.

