**Physical Function**

Body Mass Index (BMI) (i.e. weight and height) will be determined at baseline and post-intervention.

Systemic blood pressure (using a digital monitor with an automated cuff) and pulse rate will be measured at baseline.

Subjects will then complete the *International Physical Activity Questionnaire (IPAQ),* a verbally administered, 7-item questionnaire pertaining to physical activity level. This questionnaire is short and should take less than 15 minutes to administer. It has been found to have a test-retest reliability of .79 in a normal adult population. This questionnaire classifies subjects on a 3-level scale: Low, Moderate, and High Activity. These scores are assigned based on detailed instructions provided by the IPAQ. Two assessors, who are masked to all other outcomes, will independently categorize each subject as having 'low', 'moderate' or 'high' activity levels.

The “Chair sit and reach test” is used to assess lower body flexibility, which is important for good posture, for normal gait patterns and for various mobility tasks, such as getting in and out of a bathtub or car. From a sitting position at front of chair, with leg extended and hands reaching toward toes, the number of inches (cm) (+ or -) between extended fingers and tip of toe will be measured[18](#_ENREF_18).

The “30-Second Chair Stand” is used to assess lower body strength, needed for numerous tasks such as climbing stairs, walking and getting out of a chair, tub or car. Also reduces the chance of falling. The number of full stands that can be completed in 30 seconds with arms folded across chest will be measured[18](#_ENREF_18).

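### Covariates for the main intervention analysis are picked from observed baseline differences between randomised groups; a short set fixed in advance on prognostic grounds should replace that rule

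*Protocol*

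**What the plan says.** All of the analysis text is in the Protocol, under Study Statistics, in the item on the statistical plan.

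- Baseline demographics and clinical variables are to be "compared for the 2 groups using descriptive statistics and parametric or non-parametric tests as appropriate". No significance level or other threshold for a difference is given.
- The covariate rule follows: "Group differences (e.g. age, level of fitness) will be used as covariates in the main intervention analysis". The examples are introduced by e.g., so the list is open. No maximum number and no prognostic rationale is stated.
- Post-intervention group differences "will be estimated using a multivariate analysis of covariance (ANCOVA), with the baseline measures as covariates". The selected covariates come on top of these baseline measures.
- On size: "A sample size calculation is not applicable to this type of exploratory, pilot study", and "a minimum of 10 subjects is feasible to provide an indication of the acceptability of the AYT intervention". Ten is a floor; no target or maximum is stated.
- On allocation (Study Procedures, study design): subjects will "then be randomized into two equally sized groups", so 5 against 5 at the floor.

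The secondary regression of balance and fear of falling on visual function, by contrast, names age and fitness as its controls outright.

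**The concern.** Read together, the first two sentences make a selection rule: compare the randomised groups, then adjust for whatever differs. A SAP that followed the rule would inherit it, so this is a stated method and not a detail left for later.

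A baseline test between randomised groups asks whether the difference could be chance, and the answer is already known. It does not show which variables predict the outcome, which is the reason to adjust. The rule can go wrong in two ways. A prognostic variable with a moderate imbalance may be left out. A non-prognostic variable with a large imbalance may be let in, and such a variable is correlated with group by construction, so it costs precision. Because no threshold is stated, the analyst also has discretion over the model after seeing the groups.

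At stake is the precision and credibility of the estimates that the Protocol wants to use to suggest possible benefits and to plan larger trials.

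**Working it through.** The Protocol gives no alpha, power, effect size or SD, so there is no figure of its own to reproduce. The checks below show how large the cost could be.

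**Inputs from the Protocol:** minimum N = 10, 1:1 allocation, ANCOVA with baseline adjustment, open covariate list.

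**Assumptions:** two-sided 0.05 as the selection threshold; correlation 0.6 between an outcome and its baseline; slope 0.4 for a prognostic covariate (unit variance); 2, 5 or 10 candidates; N = 10, 20 or 30; each outcome adjusted for its own baseline.

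**1. Imbalance needed for selection at 5 v 5.** t(0.975, 8) × √(2/5) = 2.306 × 0.632 = 1.46 SD. Smaller imbalances would be missed under this threshold.

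**2. Variance cost of a covariate that only just qualifies.** Its squared correlation with group is R² = t²/(t² + N − 2), and it multiplies the variance of the group coefficient by 1/(1 − R²).
- N = 10: R² = 5.318/13.318 = 0.399, factor 1.66
- N = 20: factor 1.25
- N = 30: factor 1.15

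This is the geometric cost alone. A prognostic covariate also lowers residual variance, which offsets it.

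**3. Chance of at least one difference at p<0.05 under correct randomisation (independent tests).** 1 − 0.95^k = 9.8% for 2 variables, 22.6% for 5, 40.1% for 10. Correlated baseline variables would change these figures.

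**4. Residual degrees of freedom at N = 10.** Intercept, group and own baseline leave 10 − 3 = 7. Adding age leaves 6. If level of fitness means the activity questionnaire (an assumption), then "This questionnaire classifies subjects on a 3-level scale: Low, Moderate, and High Activity", which uses 2 more and leaves 4.

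**5. Simulated variance of the treatment estimate, selection versus own-baseline ANCOVA.**

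| N | Candidates | Change in variance |
|---|---|---|
| 10 | 2 | about +1% to +5% |
| 10 | 5 | about +30% |
| 10 | 10 | about +58% |
| 20–30 | 2 to 10 | −6% to +14% |

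The N = 10 cells are noisy: repeat runs gave up to +9% with 2 candidates and +53% to +66% with 10.

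**6. Selection versus pre-specifying the truly prognostic covariates, same settings.** +1% to +63%; selection was never better.

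**7. False-positive rate.** In simulations with no treatment effect, 2 or 4 candidates, slopes 0 to 0.5 and selection at p<0.05 or p<0.20, the rejection rate under selection was 3.1–5.2% at N = 10 and 2.5–5.3% at N = 20.

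**8. Limit on pre-specification.** At N = 10 with four candidates of slope 0.5 and selection at p<0.20, the variance was 0.764 for own baseline only, 0.862 with selection and 0.937 with all four fixed in advance. A fixed set helps at this size only if it is very short.

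**The case against.** The strongest defence is that adjusting for an observed imbalance protects the trials in which a prognostic variable happens to be unbalanced. That is true. At N = 20 with two candidates of slope 0.5 and selection at p<0.05, among the trials where a covariate was selected, the own-baseline model had variance 0.436 and rejected 14.6% of true nulls; the model with the selected covariate had 0.225 and 4.5%. Over all trials, however, fixing both covariates in advance gave 0.155, against 0.213 for selection and 0.234 for own baseline only. The protection is better obtained by naming the covariates.

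Second, the only covariates named are age and level of fitness, which the Protocol treats as relevant elsewhere, and with two candidates the variance penalty is small even at 10 subjects. This stands as a limit on size. It does not close the list.

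Third, the baseline comparison includes descriptive statistics, so imbalance might be judged without a test. The 1.46 SD threshold would then not apply, but discretion would be greater.

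Fourth, this is an exploratory pilot with no power claim. That limits the consequence. It does not make the rule a good one.

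A reader might go further and infer that the rule inflates the variance by half or more as a matter of course, doubles it, or raises the false-positive rate. The Protocol does not support these. The large figures need N at its floor, about ten candidates that are mostly noise, and a 0.05 cut-off, none of which it states. Type I error was not inflated under any fixed rule tried.

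**Conclusion.** The point holds as a weakness in a stated method. The covariates of the main intervention analysis depend on chance differences between randomised groups, and the model cannot be known before the data are seen.

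The cost is precision and discretion. It may be negligible (two candidates at 10 subjects) or substantial (ten candidates at 10 subjects), and at 20 to 30 subjects selection can even be slightly better than own-baseline adjustment alone. These are illustrative ranges resting on the assumed correlation, slope and threshold. The comparison with pre-specification points one way only for short sets of covariates that really are prognostic. A reader might take it as a case for adding every plausible covariate in advance, but at 10 subjects that would be worse than the present rule.

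**What to change.** Replace the covariate sentence in Study Statistics with a set fixed in advance on prognostic grounds. For example: The main intervention analysis of each outcome adjusts for the baseline value of that outcome. At most one or two further covariates, named here for their expected relation to the outcome, are included regardless of observed group differences; with about 10 subjects they are used only in a sensitivity analysis.

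Age and level of fitness are natural candidates because the Protocol already names both. If fitness is kept, state which measure is meant and whether it enters as a score or as categories.

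Keep the descriptive baseline table. Between-group baseline tests should not decide the adjustment; whether they are still reported is secondary.

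**Cost:** an edit to the text, with no new data. The present text refers to baseline measures in the plural within a multivariate model. If the sponsor meant all baselines jointly, naming one per outcome changes the model and should be a deliberate decision. The statistical downside is that a chance imbalance in an unlisted covariate stays unadjusted in the main model; the descriptive table will show it, and it can be discussed as a limitation.
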